## 1. RATIONALE

Patients with impaired glucose tolerance or diabetes have a 2 to 4 fold higher risk of developing cardiovascular disease (CVD) (1). In patients with diabetes the prevalence of myocardial infarction and heart failure is higher than in individuals without diabetes. Cardiac death is the main cause of mortality in patients with diabetes (2). After diagnostic testing 25 to 45% of patients with an acute coronary syndrome have diabetes, whereas the prevalence of diabetes in the general population varies between 10 to 15% (3). Up to 65% of patients with an acute coronary syndrome have diabetes or metabolic disturbances (3).

Both after primary percutaneous coronary interventions (PCI) and coronary artery bypass grafting (CABG), patients with diabetes have a higher risk of cardiac death (4;5) and worse left ventricular function (6). Comparing patients with newly detected type 2 diabetes to patients with previously established diabetes, both groups have comparable proportions of re-infarction, stroke, and long-term mortality following acute myocardial infarction (4). Subdividing cardiac death, the rate of sudden cardiac death in patients with diabetes is comparable to patients without diabetes, whereas heart failure is the main cause of the attributive cardiac death in patients with diabetes (7).

In acute myocardial infarction, several therapies including early primary percutaneous coronary interventions and ACE-inhibitors aim to preserve ventricular function and thereby prevent the development of heart failure (3).

Patients with impaired left ventricular function after revascularization have worse prognosis (8). Patients with metabolic disturbances or diabetes are likely to develop heart failure (9;10). Moreover, increased admission glucose levels (11) and persistent hyperglycemia (12) are related to a higher

mortality in patients with acute MI, regardless of diabetic status. These elevated glucose levels are thought to reflect pre-existent impaired glucose tolerance or increased physical stress.

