| - Heart failure                   |                | A        |
| - chest pain                      |                | B        |
| ICD implantation                  | 6              |          |
| New onset diabetes                | 7              |          |
| Prediabetes                       | 8              |          |

Tabel 1: Clinical secondary endpoints.

A non-elective hospitalization (defined as an overnight stay, with different dates for admission and discharge) for clear symptoms of heart failure within 4 months and after long-term follow-up will be recorded. Furthermore, non-elective hospitalization (defined as an overnight stay, with different dates for admission and discharge) for chest pain will be recorded as an endpoint. Implantation of an internal cardiac defibrillator (ICD) will be recorded as an endpoint. Hospitalization for other reasons than heart failure or chest pain will not be recorded as an endpoint. Whenever a patient undergoes an elective PCI, CABG, or ICD implantation, or has a recurrent myocardial infarction or stroke, the patient is (likely to be) hospitalized. Therefore, in case of these events, the hospitalization itself will not be recorded as a separate endpoint. New onset diabetes and prediabetes, as defined by the guidelines (see Appendix 14.2) will be recorded as an endpoint. Whenever new onset diabetes is

diagnosed, patients will be treated by an endocrinologist at University Medical Center Groningen according to current guidelines. Treatment for diabetes will be additional to study treatment. Visits for treatment will be separate from study visits.

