#### **9.3.4.2 Glycometabolic state**

Patients with known diabetes are those reporting on an established diagnosis or those on glucose lowering medication, and will be excluded per protocol. The study protocol asks for fasting plasma glucose and glycosylated hemoglobin in patients with unknown glycometabolic state. The glycometabolic classification, performed at hospitalization, in normal glucose regulation, impaired glucose regulation (impaired fasting glucose and/or impaired glucose tolerance), and newly detected diabetes will be based on fasting plasma glucose and glycosylated hemoglobin according to

definitions in the guidelines. In addition, an oral glucose tolerance test (OGTT) will be performed to detect the sensitivity for glucose administration.

If diabetes or prediabetes is diagnosed, according to the current guidelines (See appendix 14.2), it will be recorded as an adverse event and reported as an endpoint.

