## **11. STATISTICAL ANALYSIS AND SAMPLE SIZE**

### **11.1 Statistical analysis**

Analyses will be performed according to the intention-to-treat principle for the whole population and in the specified subgroups. An analysis per protocol will also be performed. Differences between group means will be assessed with the two-tailed Student's t-test. Chi-square analysis or Fisher's exact test is used to test differences between proportions. Survival will be calculated by the Kaplan-Meier product-limit method. The Mantel-Cox (or log-rank) test will be used to evaluate differences in survival between the two treatment groups. The Cox proportional-hazards regression model will be used to calculate relative risks and to adjust for differences in baseline characteristics. The relationship between metformin use and the primary and secondary endpoints will be studied using linear regression analysis, in which the outcome at the time of determination will be adjusted for the outcome at baseline. In addition, to assess the relationship between the determinant and the outcome over multiple measurements in time, GEE (generalized estimation equations) will be used as a method for dealing with correlated data arising from repeated measurements. Statistical significance is considered as a two-tailed p value <0.05. The Statistical Package for the Social Sciences (SPSS Inc., Chicago, IL, USA) version 16.0 will be used for all statistical analysis.

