### **11.3 Sample size**

The study is powered for the supposed change caused by the intervention in global left ventricular ejection fraction between the intervention group and placebo group at 4 months after hospitalization. This trial is primarily intended as a proof of concept study, and therefore not powered for a mortality benefit, but for the surrogate endpoint difference in left ventricular ejection fraction measured with CMR imaging 4 months after primary PCI. Van der Vleuten et al (8) demonstrated that a decrease of 5% in LVEF after STEMI leads to a HR of 1.44 for mortality at 1 year follow-up. The recently published HEBE III trial assumed a 3% change in LVEF to be clinical relevant

and to be feasible. Therefore a difference of 3% in LVEF is a relevant primary endpoint. With 141 patients in each study group, the study has 80% power to detect a 3% difference in change in ejection fraction between active treatment and control, assuming a 2-sided  $\alpha$  of .05 for the change in left ventricular ejection fraction.

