### 11.3.1 Sample size calculation

The following formula was used to assess the sample size (N) per group. The entire sample size will therefore be 2N.

$$N = (A + B)^2 \times 2 (\sigma^2 / \delta^2)$$

|            |                                            |      |
|------------|--------------------------------------------|------|
| N =        | sample size of 1 group (Total sample = 2N) | ?    |
| A =        | significance level (5%=1,96)               | 1,96 |
| B =        | power (80%=0,84)                           | 0,84 |
| $\sigma$ = | expected standard deviation                | 9    |
| $\delta$ = | delta (clinical relevant difference)       | 3    |

This results in the following calculation:

$$N = (1,96 + 0,84)^2 \times 2 (9^2 / 3^2)$$

$$N = (2,8)^2 \times 18$$

$$N = 7,84 \times 18$$

$$N = 141$$

Sample size (2N) = 282

We assumed that in 12% of patients a primary endpoint observation would not be obtained. However, actual rates of patients not undergoing cardiac MRI (primary endpoint) differ from that assumption. Actual rates are close to 26%, therefore we require an increase to 380 patients , assuming that in 26% of patients no primary efficacy measurement will be obtained.

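### The diabetes and prediabetes endpoints are not limited to diagnoses after T0, so disease already present at admission can be counted with incident cases and pull the risk ratio towards 1

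*Protocol*

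**What the plan says.** Section 5.3 lists diabetes as an exclusion. Section 9.3.4.2 describes the excluded patients as those with known diabetes, meaning a reported diagnosis or use of glucose-lowering drugs. Patients of unknown status are tested: "The glycometabolic classification, performed at hospitalization, in normal glucose regulation, impaired glucose regulation" and newly detected diabetes are the categories, based on fasting glucose and HbA1c, with an OGTT in addition. The section closes by stating that a diagnosis of diabetes or prediabetes, "according to the current guidelines (See appendix 14.2), it will be recorded as an adverse event and reported as an endpoint".

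Section 9.1.2 repeats the rule: "New onset diabetes and prediabetes, as defined by the guidelines (see Appendix 14.2) will be recorded as an endpoint". Table 1 lists new onset diabetes as class 7 and prediabetes, without the words new onset, as class 8. Appendix 14.2 gives laboratory thresholds only, with no condition on baseline status or timing. Section 2.2 states the objective as the prevalence of new onset diabetes and prediabetes. Section 9.4 schedules an OGTT at T0 and again at T3 (4 months), and glycometabolic laboratory tests at T0 to T3.

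Section 1 gives the background rate: "After diagnostic testing 25 to 45% of patients with an acute coronary syndrome have diabetes". It puts diabetes or metabolic disturbance together at up to 65%.

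**The concern.** Study drug starts within 3 hours after PCI (section 5.1). An HbA1c above the diabetes threshold during the same admission reflects the preceding weeks, so treatment can neither have caused nor prevented it. Section 1 itself attributes raised glucose in acute MI to pre-existing impaired tolerance or to physical stress. Such cases are expected at the same rate in both arms.

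If they count as endpoint events, they add the same quantity to the numerator in each arm. The risk ratio moves towards 1 and the added events contribute noise. Prevention of diabetes is one of the benefits for which section 1 argues. A diluted comparison could be read as evidence that metformin does not prevent diabetes, when most of the counted events were never preventable.

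**Working it through.** **The plan's own figures.** No sample size or power is stated for the diabetes endpoints. The figures that are stated reproduce:

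- LVEF: (1.96 + 0.84)² × 2 × (9²/3²) = 7.84 × 18 = 141.12, against 141 per arm. Allowing for 26% missing, 282/0.74 = 381.1, against 380. None of this depends on the diabetes endpoints.
- Number needed to treat for incident diabetes: 1/0.06 = 16.7, against the cited 17.

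**Share already positive at T0 (b).** The 25–45% in section 1 includes known diabetes, which is excluded here. The protocol does not give the known share. As an assumption I take 10–15%, borrowing its general-population prevalence. Among patients without known diabetes:

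- lowest: (0.25 − 0.15)/(1 − 0.15) = 0.118, about 12%
- highest: (0.45 − 0.10)/(1 − 0.10) = 0.389, about 39%

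**Control incidence over 4 months (p).** Section 1 cites a 40% relative and 6% absolute reduction over 1.8 years. That implies a control risk of 0.06/0.40 = 0.15 over 1.8 years. At constant hazard, p = 1 − 0.85^((4/12)/1.8) = 0.0296, about 3%. With a true risk ratio of 0.60, the metformin risk is 0.0178. As a generous alternative I let the whole 15% occur within the counting period.

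**Formula.** Observed risk in an arm = b + (1 − b) × incidence in that arm, with b the same in both arms. Power is for two proportions at two-sided 0.05 by normal approximation, with 190 per arm (380/2) and no missing glycaemic data. Only rejections in favour of metformin are counted, which is why some values fall below 5%. The restricted analysis uses 190 × (1 − b) per arm.

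| Control incidence | b | Control risk | Metformin risk | Apparent risk ratio | Risk difference, points | Control events already present at T0 | Power as written | Power restricted to at-risk patients |
|---|---|---|---|---|---|---|---|---|
| 3.0% | 12% | 0.1461 | 0.1357 | 0.93 | 1.04 | 82% | 4.8% | 10.6% |
| 3.0% | 39% | 0.4081 | 0.4009 | 0.98 | 0.72 | 96% | 3.5% | 8.6% |
| 15% | 12% | 0.2520 | 0.1992 | 0.79 | 5.28 | 48% | 23% | 39% |
| 15% | 39% | 0.4815 | 0.4449 | 0.92 | 3.66 | 81% | 11% | 29% |

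First row in full: 0.12 + 0.88 × 0.02965 = 0.1461; 0.12 + 0.88 × 0.01779 = 0.1357; ratio 0.929.

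At 3% incidence, the control arm would hold about 190 × 0.12 = 23 to 190 × 0.39 = 74 cases present at T0. Incident cases would number about 190 × 0.88 × 0.02965 = 5.0 down to 190 × 0.61 × 0.02965 = 3.4. Restricting to patients free of diabetes at T0 returns the risk ratio to 0.60.

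**Absolute scale.** The true difference of 1.19 points becomes 1.04 or 0.72. The true 6.0 points becomes 5.28 or 3.66. In each case the factor is exactly (1 − b).

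**Prediabetes.** If up to 65% have diabetes or metabolic disturbance, then after the same subtraction up to (0.65 − 0.15)/0.85 = 59% to (0.65 − 0.10)/0.90 = 61% could be positive for one or the other at T0. The protocol gives no incidence for prediabetes, so I compute no risk ratio for it.

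**The case against.** A reader might infer that the protocol states outright that T0 findings are new onset events. It does not. The in-hospital category is called newly detected and the Table 1 endpoint new onset, and onset ordinarily excludes disease already present. The closing sentence of section 9.3.4.2 names no visit and could refer to follow-up. Section 9.2 speaks of patients who developed diabetes during the study. This stands as far as it goes: the counting of T0 cases follows from the rule as written and is not declared. But nothing shuts them out. The sentence follows directly on an in-hospital classification, class 8 carries no new onset label, the objective speaks of prevalence, and Appendix 14.2 gives only thresholds. The adjudication committee in section 10.7, although it includes an endocrinologist, has no written ground for rejecting a T0 case.

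Section 11.1 adjusts outcomes for their baseline value by linear regression. That shows an intention to account for baseline, but it does not define an at-risk set for a binary event.

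A reader might also infer that prevalent cases always swamp incident ones and that a real effect would look null. The figures do not support that in general. At 15% incidence and b = 12%, the two kinds of case are about equal (23 and 25 in the control arm), and the absolute difference shrinks only by (1 − b). Nor can 45% serve as the undetected share, because it includes the known diabetes that is excluded.

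Finally, the T0 fasting glucose and OGTT may follow the first dose and are affected by acute stress, so T0 status is an imperfect baseline. That is a fair limit on the remedy.

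**Conclusion.** The point holds as a gap in the endpoint rule. As written, endpoints 7 and 8 can mix disease present at admission with disease arising afterwards. For diabetes, a true risk ratio of 0.60 would appear as about 0.93–0.98 at 3% control incidence over 4 months, and as about 0.79–0.92 at 15%. These ranges rest on an assumed known share of 10–15%, a constant hazard, an effect of the cited size, and equal T0 prevalence in the two arms.

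The weight is moderate. A reader might infer that the flaw threatens the trial's main conclusion; it does not. These are secondary endpoints in a study described in section 11.3 as proof of concept, and the LVEF analysis and its sample size are untouched. Power for diabetes at 4 months is about 9–11% even after restriction, against 3.5–5% as written, so a non-significant result would be likely either way. What the change restores is the meaning of the estimate.

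**What to change.** - Keep the closing sentence of section 9.3.4.2, because it is also that section's reporting rule for diagnoses at later visits, but limit its endpoint clause to diagnoses made after T0. Whether a T0 finding is also recorded as an adverse event can be settled separately.
- Report T0 glycometabolic status as a baseline characteristic. State which T0 test defines it; HbA1c is least affected by acute stress or by a first dose already given.
- Count new onset diabetes only in patients without diabetes at T0, and new onset prediabetes only in patients with normal regulation at T0.
- Align sections 2.2, 9.1.2 and 9.3.4.2 and Table 1, replacing prevalence with incidence in the objective and labelling class 8 as new onset. Give the adjudication committee the same rule.
- Do not rest the endpoint on a 1-year glycaemic result unless the T4 panel is confirmed to include one: section 9.4 lists only laboratory analysis there, and no OGTT.

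The cost is a wording change and fewer counted events. The tests needed at T0 and T3 are already scheduled.

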### **9.3.5 Skin autofluorescence**

Tissue AGE accumulation was assessed using a validated skin autofluorescence (AF) reader (advanced glycation end-products reader; patent PCT/NL99/00607;DiagnOptics BV, Groningen, The Netherlands). The AGE-reader illuminates a skin surface of approximately 2 cm^2, guarded against surrounding light, with an excitation light source between 300-420 nm (peak excitation ~370 nm). Light from the skin is measured with a spectrometer in the 420-600 nm range, using 200 µm glass fibers. The value of skin AF is calculated as the ratio of the light intensity in the 420-600 nm wavelength range and the light intensity in the 300-420 nm wavelength range. Meerwaldt et al have shown that repeated skin AF measurements on one day show an overall Altman error rate of 5.03% [78]. Intraindividual seasonal variance shows an Altman error rate of 5.87% [78]. The difference between repeated measurements does not alter depending on skin AF level [78]. Skin AF will be measured at the volar side of the lower arm at approximately 10 to 15 cm below the elbow fold. The measurement was performed three times at a healthy skin site (i.e. without visible vessels, scars or other skin abnormalities) and an average was calculated. Skin AF will be measured during hospitalization, and 4 months after randomization.

### **9.3.6 Cardiac magnetic resonance imaging**

To determine LVEF, cardiac magnetic resonance imaging (CMR) will be performed. CMR examination will be performed on a 3 Tesla clinical scanner (3T Achieva, Philips, Best, the Netherlands) at the Neuro-imaging Center (general director: [name]) using a phased array cardiac receiver coil at 4 months after primary PCI. Electrocardiogram-gated images are acquired during repeated

breath-holds of approximately 10 seconds. LV function is determined with cine imaging, using a segmented steady state free precession pulse sequence in multiple short axis views every 10 mm covering the entire left ventricle. Typical in plane resolution was 1.6 x 1.9 mm^2, with slice thickness of 6.0 mm (repetition time/echo time = 3.2/1.6 ms, flip angle 60°, matrix 256 x 156, temporal resolution 35 - 50 ms). Late gadolinium-enhanced (LGE) images are acquired to determine infarct size and transmural extent of infarction. A 2D segmented inversion recovery gradient-echo pulse sequence will be used, 15 minutes after administration of a gadolinium-based contrast agent (Dotarem, Guerbet, Roissy, France) (0.2 mmol/kg), with slice locations identical to the cine images. Typical in plane resolution is 1.4 x 1.8 mm^2, with slice thickness of 6.0 mm (repetition time/echo time = 9.6/4.4 ms, flip angle 25°, matrix 256 x 166, triggering to every other heart beat). The inversion time will be set to null the signal of viable myocardium. All MRI data are sent anonymously to independent cardiologists, who are blinded for randomization status, for quality control and blinded analysis.

### **9.3.7 Blood pressure**

Blood pressure will be measured in a seated position during physical examination using a standard mercury sphygmomanometer.

### **9.3.8 NYHA Heart Failure score**

The study physician will determine the NYHA heart failure classification score according to the criteria (see appendix, chapter 14).

### **9.3.9 Pregnancy test**

A pregnancy test, using serum human chorionic gonadotropin (HCG), will be measured in all female patients with childbearing potential (female patients of 60 years and younger) during hospital

admission and we will perform pregnancy tests during outpatient hospital visits when there is a reasonable suspicion of pregnancy.

#### 9.4 Study visits

The study visits are summarized in the study flow chart (chapter 4, page 21). All efforts will be made to perform study visits as scheduled. However, a 5-day margin will be allowed for visits T1 and T2, and a 10-day margin will be allowed for visits T3, T4 and T5. All study procedures will have to be performed during study visit as scheduled, with the exception of the CMR-scan. The CMR-scan may be performed 10 days before visit T3.

- During hospitalization (T0)
  - inclusion/exclusion;
  - primary PCI (see inclusion criteria);
  - verbal followed by written informed consent;
  - randomization;
  - dispense study drug;
  - NYHA heart failure score (see appendix, chapter 14)
  - medical history;
  - concomitant medication;
  - ECG;
  - echocardiography (diastolic function);
  - skin autofluorescence;
  - serious adverse events recording;
  - clinical examination (blood pressure, heart rate, length, weight,);

- laboratory analysis (pregnancy test for female patients of childbearing potential, regular hematology and biochemistry, plus glycometabolic state, inflammatory state, lipid and cholesterol spectrum, AGEs, renal function, and neurohormones);
- oral glucose tolerance test (OGTT);
- Visit 1 (T1) at 2 weeks:
  - concomitant medication;
  - NYHA heart failure score;
  - ECG;
  - serious adverse events recording;
  - clinical examination (blood pressure, heart rate, length, weight,);
  - laboratory analysis (pregnancy test for female patients of childbearing potential, regular hematology and biochemistry, plus glycometabolic state, inflammatory state, lipid and cholesterol spectrum, AGEs, renal function, and neurohormones).
- Visit 2 (T2) at 6-8 weeks:
  - concomitant medication;
  - dispense study medication;
  - NYHA heart failure score;
  - ECG;
  - serious adverse events recording;
  - clinical examination (blood pressure, heart rate, length, weight,);
  - laboratory analysis (pregnancy test for female patients of childbearing potential, regular hematology and biochemistry, plus glycometabolic state, inflammatory state, lipid and cholesterol spectrum, AGEs, renal function, and neurohormones).

- Visit 3 (T3) at 4 months:
  - concomitant medication;
  - stop study medication and record the amount of study drug received, dispensed, consumed or administered for drug accountability;
  - NYHA heart failure score;
  - ECG;
  - echocardiography (diastolic function);
  - skin autofluorescence;
  - CMR-scan (primary endpoint);
  - serious adverse events recording;
  - clinical examination (blood pressure, heart rate, length, weight,);
  - laboratory analysis (pregnancy test for female patients of childbearing potential, regular hematology and biochemistry, plus glycometabolic state, inflammatory state, lipid and cholesterol spectrum, AGEs, renal function, and neurohormones);
  - oral glucose tolerance test (OGTT).
- Visit 4 (T4); long-term follow-up (1-year) :
  - concomitant medication;
  - NYHA heart failure score;
  - ECG;
  - serious adverse events recording;
  - clinical examination (blood pressure, heart rate, length, weight,);
  - laboratory analysis
- Visit 5 (T5); long-term follow-up (2-year): visit to outpatient clinic or by telephone
  - concomitant medication;

- NYHA heart failure score;
- serious adverse events recording;
- length, weight.

